## Abstract

**Abstract:**

**Introduction:**

Children and young people with neurodisability (conditions affecting the brain or nervous system, creating functional impairment, eg, autism, learning disabilities, epilepsy, cerebral palsy or attention-deficit/hyperactivity disorder) have more complex health and educational needs than their peers, contributing to higher healthcare use and special educational needs (SEN) provision. To guide policy and improve services, evidence is needed on how health and education support and outcomes change with age for adolescents with and without neurodisability.

**Methods and analysis:**

Using the Education and Child Health Insights from Linked Data (ECHILD) database, which links health and education data across England, we will follow adolescents from the start of secondary school (Year 7) into early adulthood. We will classify children with and without neurodisability recorded in hospital and education records before Year 7, compare their sociodemographic characteristics and describe trends in health and educational outcomes throughout secondary school. We will estimate rates of planned and unplanned healthcare contacts by year of age (11–22 years old), and we will examine changes in trends before, during and after transition to adult healthcare. We will also estimate the proportion of adolescents with school-recorded SEN provision and rates of school absences and exclusions by year of age (11–15 years old) for the two groups. We will explore variation in outcomes by neurodisability subgroup and sociodemographic characteristics and contextualise the findings using existing interview and survey data from children, young people and parents/carers generated in the Health Outcomes of young People throughout Education (HOPE) research programme.

**Ethics and dissemination:**

Ethics approval for analyses of the ECHILD database has been granted previously (20/EE/0180). Findings will be shared with academics, policymakers and stakeholders, and published in open-access journals. Code and metadata will be shared in the ECHILD GitHub repository.

Strengths and limitations of this studyWe use linked education and health data covering all of England, providing up to 12 years of follow-up and a large sample size for analyses stratified by neurodisability subgroups and sociodemographic factors.We use both education and health data to identify children and young people with neurodisability, to increase case ascertainment compared with using health data alone.We integrate lived experience evidence from children, young people and parents/carers from the Health Outcomes of young People throughout Education (HOPE) research programme, enhancing both the validity and depth of our findings and interpretation.The Education and Child Health Insights from Linked Data (ECHILD) database does not capture National Health Service healthcare outside acute hospital settings (such as primary care or additional support services provided in special schools), or education provided outside state-funded schools.Some children with neurodisability are likely to be omitted as not all are diagnosed or identified by services by the start of secondary school and others may be missed without linkage to other datasets, such as primary care or community paediatrics.

## Introduction

 Neurodisability refers to long-term congenital or acquired conditions that affect the brain and/or neuromuscular system and create functional limitations.^1^ It encompasses a broad range of conditions, which often coexist, including autism, learning disability, epilepsy, cerebral palsy, attention-deficit/hyperactivity disorder or genetic conditions (such as Down syndrome).^1^ Conditions that result in neurodisability are likely to affect a significant proportion of children and young people, but there is limited evidence on prevalence estimates for England.

Children and young people with neurodisability are among the most frequent and intensive users of health services and have disproportionately higher rates of healthcare utilisation including hospital admissions, accident and emergency (A&E) attendances and other healthcare contacts than their peers.^2^,^9^ Transition from paediatric to adult healthcare, usually between the ages of 16 and 18, is a particularly vulnerable period when support often becomes more fragmented, with longer waiting times and higher thresholds for accessing services.^10 11^ Changes in health management and provision of support during transition from paediatric to adult care may negatively impact young people’s health and result in unmet need and unplanned healthcare contacts.^12^,^14^ Understanding how healthcare support and unplanned healthcare contacts (such as emergency admissions or A&E visits) change with age can inform better co-ordination of healthcare services for adolescents.

Young people with neurodisability are also more likely to have additional learning needs and receive special educational needs (SEN) provision compared with their peers or young people with other complex chronic conditions.^4 5 15^ Although approximately 5% of children starting primary school from 2008/2009 to 2018/2019 had a neurodisability or associated high-risk condition recorded before age 5, they represent 10% of all children with any SEN provision and 30% of those with Education, Health and Care Plans^16^ (a more intensive provision arranged and partly funded by local authorities^17^). Educational trajectories for young people with neurodisability are often interrupted due to school absences and/or exclusions,^45 15 18^,^22^ which likely contributes to lower school attainment^4 5 23^ and fewer young people with neurodisability completing secondary education.^5 24 25^ Education is a key social determinant of health and can impact young people’s future health and independence as adults.^26 27^ Better understanding of trends in school participation and SEN provision by age for young people with neurodisability can support better co-ordination between health and education services and may inform policies to increase school participation.

Despite high usage of special educational support and specialist healthcare by children and young people with neurodisability, there is a lack of evidence on changes in planned support (eg, planned hospital care, SEN provision) and adverse outcomes over time (eg, unplanned hospital admissions, school absences and exclusions). Further, there is limited evidence on how the needs of young people with neurodisability change with age. This study is the first step to understanding these inter-relationships. Using the Education and Child Health Insights from Linked Data (ECHILD) database,^28^ we will conduct longitudinal analyses of linked healthcare and education administrative data to describe how planned support and adverse outcomes change with age from adolescence to young adulthood. We hypothesise that as levels of proactive support decline, some adverse outcomes may increase. These descriptive analyses will inform future study designs evaluating the impact of support on long-term outcomes.

This Programme Development Grant (PDG) builds on previous work from the Health Outcomes of young People throughout Education (HOPE) research programme (referred to as the HOPE Study throughout), which aimed to examine variation in SEN provision and its impact on health and education outcomes for children with specific health conditions,^16^ including neurodisability.^29 30^ In this HOPE PDG, we extend the follow-up period from primary school into young adulthood and integrate new quantitative evidence on adolescent support and outcomes with findings from HOPE’s interviews and surveys from young people and parents/carers. This HOPE PDG began in August 2024 and is expected to end in January 2026. The research programme is ongoing and groundwork for developing the study cohort, including data cleaning, validation and the creation of coding algorithms to define the cohort for all objectives has begun.

### Aim and objectives

The overall aim of this study is to describe how planned support (planned hospital care, SEN provision) and adverse outcomes (unplanned hospital care, absences or exclusion from school) change from adolescence to adulthood among young people with neurodisability and their peers. Our research seeks to answer the question: How do health and education outcomes from adolescence to adulthood vary among young people with neurodisability and their unaffected peers?

The specific objectives are to:

Characterise cohorts of adolescents with neurodisability at secondary school entry using whole-country linked health and education records in England.Describe trends in planned support and adverse outcomes for adolescents and young adults with and without neurodisability in:The healthcare setting (focusing on planned and unplanned hospital contacts).Secondary schools (focusing on SEN provision, school attendance and exclusions).

## Methods and analysis

### Study design

We will develop a cohort of secondary school aged pupils using the ECHILD database, with longitudinal follow-up across health and education. Although all proposed analyses are descriptive, we will design the studies using the target trial emulation (TTE) framework,^31 32^ in line with the approach taken in the HOPE Study.^16^ The TTE framework, typically used to guide analyses of observational data to examine causal effects, involves two key steps: (1) specifying an ideal pragmatic randomised controlled trial (RCT) to address the research question of interest, and (2) defining how this RCT can be emulated as closely as possible using observational data. In the HOPE PDG, we adapted the TTE framework to guide the design of descriptive studies. This involved specifying the target population-based study, describing how it can be emulated using ECHILD data and identifying potential sources of bias (see online supplemental appendix for details of TTE for this programme).^32^ This approach helps assess potential biases arising from the use of observational data and identifies ways to mitigate them at the design stage.

### Data sources and linkage

The ECHILD database links routinely collected administrative data on health and education in England.^28^ Information on health comes from Hospital Episode Statistics (HES). HES is a national database that includes dated information on all National Health Service (NHS) acute hospital care (including inpatient, outpatient and A&E records) and mortality data.^33^ Education records are collated in the National Pupil Database (NPD) and include information from all state-funded schools on children and young people’s registrations in schools, education attainment scores, absences, exclusions and SEN provision.^34^ As part of the HOPE Study, we also enhanced the ECHILD database using open-source data on school characteristics (eg, type of school).^35^

### Study population and follow-up

We will develop a cohort of secondary school aged adolescents enrolled in state-funded schools in Year 7 (usually aged 11–12 years old) between 2008/2009 and 2014/2015. We will exclude young people who are 2 or more years outside of their expected age for their school year.

Adolescents will be followed up from 1 February (after the spring school census) in Year 7 through to Year 11 (the end of secondary school, usually aged 15–16 years old) in education records, and until aged 22 in healthcare records (due to data availability) (figure 1). Education outcomes will be measured until the end of term 1 of the 2019/2020 academic year (31 December 2019) in education records, the last full academic term before the COVID-19 pandemic. Healthcare outcomes will be measured up until 1 March 2020, just before the first COVID-19 lockdown in England, as the pandemic impacted access to school and the frequency of hospital contacts captured in ECHILD data.^36 37^

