### Defining key study measures

#### Defining neurodisability in administrative records

We propose two complementary approaches based on health and education data recorded in HES and in NPD to identify adolescents with neurodisability before the start of secondary school (Year 7), ensuring that all exposures are measured before the outcomes. Ensuring exposures are measured before outcomes reduces the risk of reverse causality, where the outcome might influence the exposures. Although this is descriptive work, maintaining this temporal sequence helps establish a clear direction of influence. Throughout the protocol, we refer to children with neurodisability recorded in HES and NPD as ‘children with neurodisability’, although we note that some children with neurodisability are likely to be omitted in the absence of linkage to other datasets (including primary care or community paediatrics) or because their difficulties have not been identified by any service.

We will use a phenotyping algorithm for indicating conditions with high risk of neurodisability from diagnostic data recorded in HES admitted patient care records developed as part of the HOPE Study.^16^ This list includes conditions such as cerebral palsy, epilepsy, autism, learning disabilities, muscular dystrophies and other neurologic conditions associated with high risk of functional impairment (such as hydrocephalus, brain tumours or indicators of infection or inflammation of the brain).^1 8 12 38 39^ We will use diagnostic data from all hospital admissions before entry to Year 7. We will examine recording of included conditions in adolescents and consult expert clinicians to derive clinically meaningful subgroups of conditions with comparable health and educational needs and functional impairment. These subgroups could include: (1) intellectual and developmental disorders; (2) autism spectrum disorder; (3) cerebral palsy; (4) epilepsy; and (5) genetic and chromosomal conditions.

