As adolescents with neurodisability receive much of their care outside of secondary healthcare settings (ie, in community paediatrics, primary care), some conditions are likely to be under-reported in hospital records (eg, autism or hyperkinetic disorders).^12 40^ We will therefore complement information from hospital records with information on types of need for SEN provision recorded during primary school to increase case ascertainment. This approach has been used previously in linked health and education data from Scotland^18 41^ and in studies based on education data only in England.^20 42 43^ We will examine recording of likely autism and learning disabilities using information on primary and secondary type of need for SEN provision in primary school records (Years 1–6, aged 5/6–10/11 years old). Learning disabilities will be indicated by combining three types of SEN (categorised in an ascending hierarchy): (1) profound and multiple learning difficulties (where children are likely to have severe and complex learning difficulties as well as a physical disability or sensory impairment); (2) severe learning difficulties (where children are likely to need support in all areas of the curriculum and associated difficulties with mobility and communication); and (3) moderate learning difficulties.^17^ We only use information on type of need collected prior to 2014/2015 education reforms (see figure 1),^17^ ensuring consistency of coding of SEN need over time.

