### Statistical analysis

#### Objective 1: descriptive analysis

We will derive point prevalence of neurodisability at the start of Year 7 (defined as the number of pupils with a hospital or school record of neurodisability at any point before they entered Year 7 divided by the number of pupils enrolled in Year 7), overall and by neurodisability subgroup. Children with neurodisability are more likely to live in more socioeconomically disadvantaged households, experiencing multiple social determinants of health which may affect their underlying health needs as well as their access to support services. We will describe numbers and percentages for adolescents according to baseline sociodemographic characteristics (table 2) to understand potential overlaps in factors contributing to health inequalities. NPD and HES are likely to capture adolescents with different levels of health need, we will therefore also describe the overlap and baseline characteristics of adolescents with neurodisability captured in education and health datasets. We will also compare mortality rates in adolescents with neurodisability, overall and according to data source used as a crude measure of complexity of health needs.

ECHILD does not capture termly data on children and young people educated in the private sector (approximately 7% of pupils in England each year).^34^ We will estimate the number of adolescents lost at the start of Year 7 due to being educated outside of state-funded schools. This is defined as the difference in the number of pupils ever enrolled in state-funded primary school and alive in Year 7 and the number of adolescents enrolled in Year 7.

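### Pupils who join the state system at Year 7 may have no earlier records in which neurodisability could appear, yet they count in the prevalence denominator and, if not identified, as peers

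*Protocol article*

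**What the plan says.** Under Study population and follow-up, the article takes a "cohort of secondary school aged adolescents enrolled in state-funded schools in Year 7" between 2008/2009 and 2014/2015. The one exclusion given there concerns age: "We will exclude young people who are 2 or more years outside of their expected age for their school year". No earlier enrolment is asked for.

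Under Defining neurodisability in administrative records there are two routes to a positive classification:

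- Hospital: "We will use diagnostic data from all hospital admissions before entry to Year 7".
- School, for likely autism and learning disabilities: "primary and secondary type of need for SEN provision in primary school records (Years 1–6, aged 5/6–10/11 years old").

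Data sources and linkage sets the reach of both. The database "links routinely collected administrative data on health and education in England", and the pupil records "include information from all state-funded schools on children and young people’s registrations in schools".

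Under Objective 1: descriptive analysis, point prevalence is the number of pupils with a hospital or school record of neurodisability before Year 7, "divided by the number of pupils enrolled in Year 7". It is planned overall and by neurodisability subgroup. The same section describes pupils by the baseline characteristics in Table 2, which include first language, ethnic group and area deprivation.

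**The concern.** Eligibility is judged at Year 7, while neurodisability is judged from earlier years, and nothing ensures that a pupil could have been observed in those years. For a pupil with a normal primary history in England, the absence of a record is imperfect but real evidence. For a pupil who arrives at Year 7 from abroad it is close to no evidence, because neither source could usually have held a record. A pupil from a private primary or home education in England can still be found through an admission but not through the school route. The article introduces that route because hospital data under-report conditions such as autism.

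The main stake is Objective 1, the prevalence at Year 7 and the sociodemographic profile of affected pupils. If late entry is more common in some language or ethnic groups, their pupils would be under-represented among recorded cases for a reason unrelated to neurodisability. The Table 2 indicators of health complexity (earlier chronic conditions and Year 6 contacts) rely on the same earlier hospital data, so a pupil arriving from abroad would also tend to look healthy at baseline. A second, smaller stake is that some affected pupils sit in the peer group for Objective 2.

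**Working it through.** The article states no prevalence for this cohort and no share of Year 7 entrants without earlier records, so there is no figure to reproduce. The check is misclassification algebra with the unknowns left as ranges.

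**Inputs**

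- p: prevalence that full look-back would record, taken as equal in entrants and other pupils. Illustrated at 5% and 10%. The Introduction gives about 5% for conditions recorded before age 5 in children starting primary school. That is a different population and serves only as an anchor.
- m: share of Year 7 pupils with no state primary record in Years 1–6. Not in the documents. Assumed 1–5% overall, and 20–30% in a group with many late entrants.
- s: ascertainment in those pupils relative to pupils with full look-back. Not in the documents. Assumed 0 (no route works) to 0.5 (hospital records find half of what full look-back would).
- R: true rate ratio, affected versus unaffected. Illustrated at 3.

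**Prevalence**

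Recorded prevalence = p(1 − m) + p·m·s = p[1 − m(1 − s)], so the relative shortfall is m(1 − s), whatever p is.

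| Setting | m | s | Relative shortfall | 5% recorded as | 10% recorded as |
|---|---|---|---|---|---|
| Overall | 1% | 0.5 | 0.5% | 4.98% | 9.95% |
| Overall | 1% | 0 | 1% | 4.95% | 9.9% |
| Overall | 5% | 0.5 | 2.5% | 4.88% | 9.75% |
| Overall | 5% | 0 | 5% | 4.75% | 9.5% |
| Many late entrants | 20% | 0.5 | 10% | 4.5% | 9.0% |
| Many late entrants | 20% | 0 | 20% | 4.0% | 8.0% |
| Many late entrants | 30% | 0.5 | 15% | 4.25% | 8.5% |
| Many late entrants | 30% | 0 | 30% | 3.5% | 7.0% |

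The bias is downward whenever s is below 1.

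**Rate ratios**

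Affected share of the peer group: c = p·m(1 − s) / (1 − recorded prevalence). Observed ratio = R / [1 + c(R − 1)].

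- p = 5%, m = 5%, s = 0: c = 0.0025 / 0.9525 = 0.26%. Observed ratio = 3 / (1 + 0.0026 × 2) = 2.98.
- Extreme case, p = 10%, m = 30%, s = 0: c = 0.03 / 0.93 = 3.2%. Observed ratio = 3 / (1 + 0.032 × 2) = 2.82.

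**Existing check**

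Objective 1 estimates pupils lost at Year 7, as those ever in state primary and alive in Year 7 minus those enrolled in Year 7. This looks at leavers, not entrants. Unless the Year 7 count is limited to pupils with a primary record, entrants offset leavers in that difference.

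**The case against.** The other side has five fair arguments.

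- **Part of the gap is disclosed.** The limitations state that education outside state-funded schools is not captured and that some affected children will be omitted. The text also ties its use of the term neurodisability to what is recorded in the two sources. This stands for the data gap. It does not cover the consequence for classification, or arrivals from outside England: the stated reasons for omission are conditions not yet identified or visible only in other datasets, not a missing observation window.
- **Prevalence by language or ethnic group is not a listed output.** This stands. A reader might infer, from assumed shares of 30% in pupils with another first language and 2% in others, that equal prevalence would be reported as a ratio of 0.70/0.98 = 0.71. The documents do not support that. They give neither share, the figure sets s = 0 for everyone, and only overall and neurodisability-subgroup prevalence is planned. What remains is possible distortion of the baseline profile.
- **Hospital records will find some entrants.** This stands for those schooled privately or at home in England, and is why s is carried above.
- **Restricting the main cohort has a price.** This also stands. It drops entrants positively identified in hospital data and narrows a cohort meant to describe Year 7 pupils nationally.
- **The appendix on sources of bias is not shown and may discuss this.** That is possible, but the eligibility rule and the prevalence denominator are set in the article itself.

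**Conclusion.** The concern holds in limited form. The direction follows from the article's own rules: pupils without earlier records stay in the denominator with a reduced or absent chance of entering the numerator, so recorded prevalence is too low relative to what full look-back would show. The size rests on assumptions. The overall shortfall is about 0.5–5% in relative terms for m = 1–5% and s = 0–0.5, and 10–30% in any group with m = 20–30%. That such groups align with first language or ethnic group is a reasonable inference, but Table 2 lists no migration variable, so it cannot be shown from the document.

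A reader might also conclude that the comparison of affected pupils with peers is seriously contaminated. It is not: a true ratio of 3 becomes 2.98 in the overall scenario and 2.82 in an extreme one. Nor do the documents show that the main cohort definition must change. This is a structural bias that can be measured and reported at little cost.

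**What to change.** 1. Flag every Year 7 pupil with no state-funded primary census record in Years 1–6.
2. Report how many there are, and their characteristics by first language, ethnic group and deprivation.
3. Repeat prevalence, the baseline profile and the main comparison of affected pupils with peers, restricted to pupils with an earlier primary record, and show these beside the all-Year-7 results. The sponsor should state in advance which set is primary; either is defensible.

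The cost is a derived flag, one extra analysis run and a sentence or two of protocol text. State primary enrolment is already used in Objective 1 to count pupils lost before Year 7. The restricted estimates will not cover pupils who enter the state system at Year 7. One primary record is also only a minimum: a pupil who arrived in Year 6 would pass with little look-back, so the restriction reduces the problem and does not fully remove it.

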#### Outcome: educational outcomes

We will describe changes in educational support (measured as school-recorded SEN provision) and school participation (measured by absences and exclusions from school) per year of age across secondary school (between start of Year 7 and end of Year 11, or until loss of follow-up, death or 31 December 2019, whichever occurred first) for adolescents with neurodisability and unaffected peers. Our primary focus will be on persistent absences. Secondary outcomes will be medical/non-medical absences and exclusions. All outcomes are defined in table 1.

**Table 1 T1:** Definitions of educational outcomes

Outcomes		Definition	Dataset(s)	Measured
**School participation**	Persistent absentees	Pupils who miss 10% or more of their possible sessions^45^	NPD School Census	Year 7–Year 11 (11/12–15/16 years old)
	Absence for medical reasons	Authorised/unauthorised absences for doctor/dentist appointments or illness*		
	Absences for non-medical reasons	Authorised/unauthorised absences for all other reasons than medical*		
	Exclusions	Pupils with at least one suspension (fixed-period exclusion) or permanent exclusion in the given school year		
**Educational support**	SEN provision (by type)	SEN provision will be grouped in the following descending hierarchy: No SEN provision SEN support in mainstream school EHCP in mainstream school Enrolment in specialist provision		

* We will use the total number of possible sessions rather than pupils as denominator.

EHCP, Education, Health and Care PlanNPD, National Pupil Database; SEN, special educational needs

NPD data include some information about post-16 educational outcomes (such as special school attendance until 19 years old or education, employment or training at 17–18 years from National Client Caseload Information System),^34^ and we will explore the feasibility of using these data to examine educational trajectories of adolescents with neurodisability after secondary school.

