#### Objective 2b: trends in educational support, school attendance and exclusions

We will calculate and plot the proportion of pupils experiencing each educational outcome (defined as the number of pupils with at least one recording of the outcome divided by the number of pupils on school roll at the start of the given school year) by year of age. We will use a Poisson or logistic regression model to quantify the differences between adolescents with neurodisability and their peers. The models will include age, birth year and an indicator of neurodisability, and we will account for repeated measures per child. We will also graphically quantify changes in proportions of adolescents experiencing each outcome according to neurodisability subgroup and sociodemographic characteristics (separately for adolescents with neurodisability and their peers).

Analyses carried out for objectives 2a and 2b will reveal whether support and adverse outcomes across health and education follow similar trajectories with age for adolescents with neurodisability and their peers and illustrate potential inequalities in support and adverse outcomes to inform design of further studies.

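### Education follow-up has two stated start points, 1 February of Year 7 and the start of Year 7; if the February date is applied, the exclusion trend shows a false rise from Year 7 to Year 8

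*Protocol article*

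**What the plan says.** Under Study population and follow-up: "Adolescents will be followed up from 1 February (after the spring school census) in Year 7 through to Year 11". The same sentence ties this period to education records, so the date is not confined to hospital data.

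Under Outcome: educational outcomes, support and participation are described "between start of Year 7 and end of Year 11, or until loss of follow-up, death or 31 December 2019", whichever comes first.

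Table 1 defines exclusions as "Pupils with at least one suspension (fixed-period exclusion) or permanent exclusion in the given school year". Under Objective 2b, the numerator of the plotted proportion is "the number of pupils with at least one recording of the outcome". The denominator is a roll count fixed at one time point; in the article's words, the numerator is "divided by the number of pupils on school roll at the start of the given school year". The regression terms named there are age, birth year and neurodisability, with allowance for repeated measures. Observed time is not among them.

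The absence outcomes are built differently. Persistent absentees are "Pupils who miss 10% or more of their possible sessions". For medical and non-medical absence the Table 1 footnote says: "We will use the total number of possible sessions rather than pupils as denominator". Persistent absence is the primary education focus; exclusions are secondary.

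The health side has the same split. Mortality follow-up starts on 1 February of Year 7, while the healthcare contacts section counts person-years from the start of Year 7.

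**The concern.** A proportion of pupils with at least one event grows with the length of time observed. It can be compared across school years only if each year is observed for the same length of time. Under the February rule, the Year 7 numerator would hold only events from February onwards, while the denominator stays the roll at the start of the year. Years 8 to 11 would be complete.

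Year 7 is the first of five school-year points. A low first point would look like a rise in exclusions early in secondary school, in both groups. The Introduction hypothesises that some adverse outcomes may increase as support declines, so an artefact in that direction could be read as evidence for the hypothesis.

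**Working it through.** The article states no exclusion rate, so there is no figure of its own to reproduce. The check asks what the February rule would do if the true yearly proportion were flat.

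**Inputs from the article.** Two candidate starts (1 February or start of Year 7); the at-least-one definition; the start-of-year roll as denominator; education cut-off on 31 December 2019; entry cohorts 2008/2009 to 2014/2015.

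**Assumed inputs.** End of the school year, true yearly proportion p (2% to 20%), and clustering of exclusions within pupils (none, or strong: negative binomial with k = 0.1).

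**Step 1: share of Year 7 observed, f.**
- 1 September to 22 July: 171 of 324 days = 0.53.
- 1 September to 31 August: 211 of 364 days = 0.58.
- By school weeks: 19 to 21 of 39 = 0.49 to 0.54.
- By school days, assuming 190 with 94 before February: 96/190 = 0.505.

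The range used is 0.45 to 0.58.

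**Step 2: constant rate, no clustering.** The Year 7 proportion is q = 1 − (1 − p)^f, and the false Year 8/Year 7 ratio is p/q. At f = 0.53:

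| True p | Plotted Year 7 | Ratio |
|---|---|---|
| 2% | 1.07% | 1.88 |
| 5% | 2.68% | 1.86 |
| 10% | 5.43% | 1.84 |
| 20% | 11.15% | 1.79 |

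Over f = 0.45 to 0.58 the ratio runs from 1.65 to 2.21.

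**Step 3: strong clustering.** With mean m = k((1 − p)^(−1/k) − 1), the Year 7 proportion is q = 1 − (1 + f·m/k)^(−k). At p = 5%, f = 0.53, k = 0.1: m = 0.067, q = 2.99%, ratio 1.67. Over the full grid the ratio runs from 1.24 (p = 20%, f = 0.58) to 2.09 (p = 2%, f = 0.45).

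At f = 0.505, a flat 5% is plotted in Year 7 as 2.6% without clustering and 2.9% with it.

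**Step 4: start of Year 7 instead.** Then f = 1, q = p and the ratio is 1.00.

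**Step 5: is there a matching cut at the end?** No. The last cohort (Year 7 in 2014/2015) finishes Year 11 in summer 2019 on normal progression, before 31 December 2019.

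**Step 6: group comparison within Year 7 (f = 0.53).** At constant rates, 10% versus 5% moves from 2.00 to 2.03, and 20% versus 5% from 4.00 to 4.16. With k = 0.1 in both groups the shift is larger: 6.65/2.99 = 2.22 and 15.53/2.99 = 5.19. Only the Year 7 contrast is affected.

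**Step 7: absence outcomes.** Both use possible sessions, so a shorter window shortens numerator and denominator together. In a simulation of persistent absence (beta-distributed propensity, spells of 2 to 3 days, 96 versus 190 days), the Year 7 proportion changed by about +5% to +7% relative at mean absence 5%, and by about −1% at 8%.

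**The case against.** The strongest reply is that the text specific to these outcomes already implies a whole Year 7. The education outcomes section counts from the start of Year 7, Table 1 speaks of the given school year, and the Objective 2b denominator is the roll at the start of that year. On this reading, 1 February is a general cohort-entry date and nothing is biased. This stands as far as it goes: a reader might infer that the trial will analyse a half Year 7, and the article does not support that. Start dates may also be set out in Figure 1 or the online appendix, neither of which is shown. The contradiction still stands, because the February sentence expressly covers education records and no text says which rule governs.

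A reader might also infer that the education trends in general are distorted. That is not supported. Exclusions are secondary, the session-based outcomes are not mechanically halved, and SEN provision is not shown to be affected. Nor does the article call Year 7 the reference for change with age.

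Finally, Objective 2b plots by year of age. If that means literal age and not school year, the shortfall is spread over ages 11 and 12 and is not a clean step between Year 7 and Year 8. It is diluted, not removed.

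**Conclusion.** The article contradicts itself on when education follow-up begins. The consequence is conditional: only if 1 February is applied does a flat exclusion trend show a false Year 8/Year 7 ratio of roughly 1.2 to 2.2, in both groups. The direction is the same across every calendar, rate and clustering value tried; the size depends on those assumptions, none of which come from the article.

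The damage is to the age trend in one secondary outcome. The neurodisability-versus-peer ratio is little affected at constant rates, and moves noticeably only for Year 7 under strong clustering combined with a large group difference. Persistent absence changes little. The point deserves correction before coding because describing change with age is the study's stated aim.

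**What to change.** Amend Study population and follow-up so that Year 7 education outcomes are measured over the whole school year, as the education outcomes section implies and as in Years 8 to 11. Neurodisability is still identified before Year 7, so exposure continues to precede outcome.

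State one start date per outcome and use it consistently in the population, mortality, healthcare contacts, education outcomes and Objective 2b sections. Simply reserving 1 February for hospital and mortality follow-up would not be enough, because the healthcare contacts section counts person-years from the start of Year 7.

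If 1 February is kept for education, either begin the exclusion trend at Year 8 or use observed time as an offset. The offset fits a Poisson or complementary log-log model more naturally than a logistic one, and it corrects fully only at a constant rate without clustering, so starting at Year 8 is cleaner.

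The cost is a sentence of wording, matching edits to the other sections and a date rule in the code. There is one small downside to whole-year measurement: autumn-term Year 7 events are counted for pupils known to be in the cohort only through the later spring census.
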